## 11.1.2 Hypotheses and Statistical Methods for the Immunogenicity Endpoints

### 11.1.2.1 Hypotheses

No statistical hypotheses will be tested for the immunogenicity endpoints analysis.

### 11.1.2.2 Statistical Analysis

#### 11.1.2.2.1 Immunogenicity Analysis of the Primary Series Vaccination

The point estimates and their 95% CI of the parameters corresponding to the following endpoints will be presented for each vaccine formulation and age group (a total of 8 groups):

##### ***HI titersa (1/dil) with Turkey or Horse Erythrocytes:***

- Proportion of subjects with a detectable titer (i.e. titer  $>10$  [turkey] or  $>8$  [horse] [1/dil]) on D0b, D21, and D42.
- GM of titers on D0, D21, D42.
- GM of individual titers ratio (GMTR) D21/D0, D42/D0, and D42/D21.
- Proportion of subjects with a titer  $\geq 40$  (turkey) or  $\geq 32$  (horse) (1/dil) at D0, D21, and D42.
- Seroconversion (defined as initially seronegative subjects, i.e. with  $<10$  [turkey] or  $<8$  [horse] [1/dil] pre-vaccination titer, with a post-vaccination titer  $\geq 40$  [turkey] or  $\geq 32$  [horse] [1/dil])

or

- Significant increase rate (defined as initially seropositive subjects i.e. with  $\geq 10$  [turkey] or  $>8$  [horse] [1/dil] pre-vaccination titer, with at least a four-fold increase in post-vaccination titer) from D0 to D21, D0 to D42 and from D21 to D42.

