## **8 Assessments Methods and Endpoints**

### **8.1 Immunogenicity Endpoints and Assessments Methods**

#### **8.1.1 Endpoints**

##### ***Immunogenicity***

Anti- HA Ab titers against the A/H5N1 strain will be expressed as described below (the assay will be performed using horse erythrocytes for all subjects and using turkey erythrocytes for subjects in Group 1 and Group 2; anti-HA titers will not be measured using turkey erythrocytes for Group 3 due to the extra blood sample volume that would be required):

- HI titer obtained in duplicate on D0, D21, and D42, and summarized at the subject level by individual GMs of duplicates at each timepoint. The following endpoints will be derived:
  - Individual titer ratios D21/D0, D42/D0, and D42/D21.

- Proportion of subjects with a titer  $\geq 40$  (turkey) or  $\geq 32$  (horse) 1/dilution (dil) on D0, D21 and D42.
  - Seroconversion (for subjects with a titer  $< 10$  [turkey] or  $< 8$  [horse] [1/dil] on D0: post-injection titer  $\geq 40$  [turkey] or  $\geq 32$  [horse] [1/dil])
- or
- Significant increase (for subjects with a titer  $\geq 10$  [turkey] or  $\geq 8$  [horse] [1/dil]:  $\geq$ four-fold increase of the titer) on D21 and D42.
- SN titer obtained in duplicate on D0, D21, and D42 and summarized at the subject level by individual GMs of duplicates at each timepoint. The following endpoints will be derived:
    - Individual titer ratios D21/D0, D42/D0, and D42/D21.
    - Two- and four-fold increase from D0 to D21 and to D42.

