##### *HI Test*

For HI [turkey] 12 two-fold dilutions of the 1:10 dilution of serum sample (or quality control sera) are performed and incubated with the HA antigen suspension (previously titrated to adjust the dilution at 4 HAU [HA units]/25  $\mu$ L). The HA antigen is not added to the well dedicated to each serum quality control. For HI [horse] the starting dilution is 1:8.

The mixture is incubated for 1 hour at room temperature and 25  $\mu$ L of the 0.4% RBC suspension are added. The reaction is left for 1 hour at room temperature before reading.

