##### ***Seroneutralization (1/dil):***

- Proportion of subjects with detectable neutralizing Ab (i.e. SN titer  $\geq 20$  [1/dil]) on D0c, D21, and D42.

---

a Individual geometric means of duplicates

b In order to check the baseline naïve immunogenicity

c In order to check the baseline-naïve immunogenicity

- GM of SN titer on D0, D21, and D42.
- GMTR: D21/D0, D42/D0, and D42/D21.
- Two- and four-fold increase rate from D0 to D21, from D0 to D42 and from D21 to D42.

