#### 11.1.2.2.4 Pre-booster Antibody Persistence

For each serological method, the statistical analysis will be restricted to:

- Proportion of subjects with detectable titer (for HI method: titer  $>10$  [turkey] or  $>8$  [horse] [1/dil] and for SN method: titer  $\geq 20$  [1/dil]) on D90, M3 and M6 or at M3, M6 and M12.
- GM of titers on D90, M3 and M6 or at M3, M6 and M12.
- Proportion of subjects with a HI titer  $\geq 40$  (turkey) or  $\geq 32$  (horse) (1/dil) on D90, M3 and M6 or at M3, M6 and M12.

The kinetics of the Ab titers assessed by HI, methods will be studied and summarized graphically:

- GM of anti-HA titers (HI method using horse or turkey erythrocytes) at M3 and M6 or at M3, M6 and M12 (*depending on the booster vaccination timing option*).

- GM of Ab titers (seroneutralisation method) at M3 and M6 or at M3, M6 and M12 (*depending on the booster vaccination timing option*).

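### Section 11 leaves a horse-HI pre-titer of exactly 8 in neither response branch and counts first-dilution HI readings as undetectable, against the protocol's own endpoint definitions

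*Protocol*

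**What the plan says.** **Response rule, analysis section.** In Section 11.1.2.2.1 the seroconversion branch covers subjects "with $<10$ [turkey] or $<8$ [horse] [1/dil] pre-vaccination titer". The significant-increase branch covers "initially seropositive subjects i.e. with $\geq 10$ [turkey] or $>8$ [horse] [1/dil] pre-vaccination titer, with at least a four-fold increase in post-vaccination titer". The turkey pair meets at 10. The horse pair is strict on both sides of 8.

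**Response rule, endpoint sections.** The Synopsis and Sections 2.1 and 8.1.1 define the same endpoint inclusively: "Significant increase (for subjects with a titer $\geq 10$ [turkey] or $\geq 8$ [horse] [1/dil".

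**Detectable titer.** Section 11.1.2.2.1 lists "Proportion of subjects with a detectable titer (i.e. titer $>10$ [turkey] or $>8$ [horse] [1/dil]) on D0", D21 and D42. Its footnote gives the purpose of the D0 rate: "In order to check the baseline naïve immunogenicity". Section 11.1.2.2.4 repeats the strict cut-offs for persistence: "Proportion of subjects with detectable titer (for HI method: titer $>10$ [turkey] or $>8$ [horse] [1/dil". For seroneutralization (SN), both sections use an inclusive cut-off of 20.

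**Assay.** Section 8.1.2.1 starts turkey HI from a 1:10 dilution and adds: "For HI [horse] the starting dilution is 1:8". The titer is the highest reciprocal dilution with complete inhibition. The final value is the geometric mean (GM) of duplicates no more than one two-fold step apart. Section 8.1.3 halves only values strictly below the lower limit of quantification (LLOQ).

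**Booster.** The booster definitions in the Synopsis and Sections 2.1 and 8.1.1 use below 10 and at least 10, with no separate horse cut-off. Section 11.1.2.2.5 says the booster analysis will be similar to that of Section 11.1.2.2.1.

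**The concern.** A titer of 8 in horse HI is a positive reading at the first dilution, an ordinary assay result. Under Section 11.1.2.2.1 such a subject can be neither seroconverted nor significantly increased, whatever the later titer, and the protocol does not say whether the subject stays in the denominator. Under Sections 2.1 and 8.1.1 the same subject is seropositive and responds on reaching 32.

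The detectable rule is a separate fault. It treats a positive first-dilution reading as no antibody, and it disagrees with the seropositive cut-off for turkey HI in the same list. The D0 detectable rate is meant to reveal pre-existing antibody. Section 5.2 gives likely earlier infection with avian H5N1 strains among children in the region as a reason for choosing Thailand, so a rule that can only hide low positives weakens a relevant check.

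Horse HI is the only HI assay run in all 240 subjects and the only one in Group 3.

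**Working it through.** The protocol gives no figure for these rates. Its one computed design figure (Section 11.3) reproduces: 1 − 0.99^240 = 91.0% and 1 − 0.99^120 = 70.1%, against the stated >90% and 70%. It does not depend on the HI cut-offs.

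**Step 1: which titers can occur.** Inputs are first dilutions of 8 (horse) and 10 (turkey), two-fold steps, and duplicates at most one step apart (Section 8.1.2.1). Replicates below the first dilution are set to half of it; this assumes the LLOQ equals the first dilution, since the HI LLOQ is not stated. The final titer is √(a × b).

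- Horse: √(4×4) = 4; √(4×8) = 5.66; √(8×8) = 8; √(8×16) = 11.31; then 16 and up.
- Turkey: √(5×5) = 5; √(5×10) = 7.07; √(10×10) = 10; √(10×20) = 14.14; then 20 and up.

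**Step 2: classify the horse pre-titers.**

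| Pre-titer | Section 11.1.2.2.1 | Sections 2.1, 8.1.1 | Post-titer needed for response |
|---|---|---|---|
| 4, 5.66 | seronegative | seronegative | 32 |
| 8 | neither | seropositive | 4 × 8 = 32 under the endpoint rule; none possible under Section 11 |
| 11.31 | seropositive | seropositive | 4 × 11.31 = 45.2 |

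Only 8 is affected. The two branches were evidently built to join there, because four times 8 is 32 and four times 10 is 40, the post-titer thresholds of the seronegative branch.

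**Step 3: classify detectability.** Horse 8 and turkey 10 are positive readings but fail >8 and >10. Turkey 10 meets the seropositive cut-off (≥10) and fails the detectable one.

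**Step 4: effect on the response rate in one cell of 30.** Assume 20 of 30 respond under the endpoint rule: 66.7% (95% Clopper-Pearson CI 47.2 to 82.7). Let k subjects have a pre-titer of 8.

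| k | Would respond, kept as non-responders: (20 − k)/30 | Would respond, dropped: (20 − k)/(30 − k) | Would not respond, dropped: 20/(30 − k) |
|---|---|---|---|
| 1 | 63.3% | 65.5% | 69.0% |
| 2 | 60.0% | 64.3% | 71.4% |
| 3 | 56.7% | 63.0% | 74.1% |
| 6 | 46.7% | 58.3% | 83.3% |

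The rate falls or rises according to how the subject is handled. No handling moves it by more than k/30, or 1/30 = 3.3 points per subject.

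**Step 5: effect on the detectable rate in one cell of 30.** A cell reported as 0/30 (CI 0 to 11.6%) becomes, with k subjects at the first dilution, 1/30 = 3.3% (0.1 to 17.2), 2/30 = 6.7% (0.8 to 22.1) or 3/30 = 10.0% (2.1 to 26.5). The direction is fixed: the strict sign can only lower the rate.

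**Step 6: booster definitions.** With below 10 and at least 10 applied to horse HI, a pre-booster titer of 8 is seronegative and responds at 32, the same threshold as four-fold from 8. That text leaves no gap. Only the label differs from the ≥8 rule.

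**The case against.** - **The endpoint definitions already settle the response rule.** Three places give at least 8, and Section 11.1.2.2.1 presents itself as reporting parameters of those endpoints. A programmer who follows them classifies a titer of 8 correctly. This stands as a reason to call the fault a one-symbol contradiction. It does not remove it, because Section 11 is the text that specifies the analysis.
- **The strict detectable rule is at least consistent.** Both Section 11 lists use it, detectability is not among the HI endpoints in Sections 2.1 and 8.1.1, and the HI LLOQ is not given. An LLOQ of 20 (turkey) and 16 (horse) would set low values to 20/2 = 10 and 16/2 = 8, and a strict sign would then make sense. But no subject could then have a pre-titer below 10 or below 8, and the seroconversion branch would be empty. The strict rule therefore does not fit the protocol's own definition of seronegative.
- **A lost underline in the PDF text.** This cannot be fully excluded. The strict sign does appear in two sections, and beside an intact ≥ in the same sentence.
- **Booster response.** A reader might infer that the gap at 8 carries into the booster response because Section 11.1.2.2.5 refers back to Section 11.1.2.2.1. The documents do not support that as a certainty: the explicit booster definitions leave no gap, and the later section says only that the analysis will be similar. What stands is that the two rules are not aligned.
- **Nothing is tested.** Section 11 tests no hypotheses, and the sample size rests on adverse-event detection alone. This stands and limits the seriousness.

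**Conclusion.** The protocol is wrong as written in two linked places. The horse-HI response rule in Section 11.1.2.2.1 leaves a pre-titer of exactly 8 unclassified, against its own endpoint definitions. The detectable cut-offs in Sections 11.1.2.2.1 and 11.1.2.2.4 exclude positive first-dilution readings in both assays.

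The detectable rates at D0, D21, D42 and the persistence visits can only be understated. The response rates for D0 to D21, D0 to D42 and D21 to D42 can move in either direction. A reader might infer that every affected rate comes out too low; that does not hold for the response rate, because the protocol does not say how an unclassified subject is counted.

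The size is up to about 3.3 points per affected subject in a cell of 30. The documents do not give the number of subjects at exactly 8 or 10, so no overall figure can be stated, and with none nothing changes. GM titers, GM titer ratios, the proportions at or above 32 or 40, and all SN endpoints are unaffected. In persistence only the detectable line is touched. The result rests on the LLOQ being the first dilution. This is a low-cost correction to descriptive analyses.

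**What to change.** - In Section 11.1.2.2.1, define initially seropositive as a titer of at least 10 (turkey) or at least 8 (horse), as in Sections 2.1 and 8.1.1. Every titer then falls in one branch and the denominator question disappears.
- In Sections 11.1.2.2.1 and 11.1.2.2.4, define a detectable HI titer as at least 10 (turkey) or at least 8 (horse). No correct version exists elsewhere in the protocol, so both places need the change.
- In the booster definitions of the Synopsis and Sections 2.1 and 8.1.1, add the horse cut-off (below 8 / at least 8) beside the turkey one (below 10 / at least 10), so that they agree with the rule Section 11.1.2.2.5 carries over.

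The cost is a wording change and the matching program lines, best made before the first partial database lock. No further data or subjects are needed.

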##### ***Seroneutralization (1/dil):***

- Proportion of subjects with detectable neutralizing Ab (i.e. SN titer  $\geq 20$  [1/dil]) on D0c, D21, and D42.

---

a Individual geometric means of duplicates

b In order to check the baseline naïve immunogenicity

c In order to check the baseline-naïve immunogenicity

- GM of SN titer on D0, D21, and D42.
- GMTR: D21/D0, D42/D0, and D42/D21.
- Two- and four-fold increase rate from D0 to D21, from D0 to D42 and from D21 to D42.

#### 11.1.2.2.2 Methods for Statistical Analysis

##### *For all titration methods*

Geometric mean computation: Assuming that the  $\text{Log}_{10}$  transformation of the measurements follows a normal distribution, at first, the mean and 95% CI will be calculated on  $\text{Log}_{10}$  measurements using the usual calculation for normal distribution, then antilog transformations will be applied to the results of calculations, in order to provide GMs and their 95% CIs.

95% CIs computation will be performed according to:

- The normal approximate method for CIs of GMs (GMTs and GMTRs).
- The exact binomial distribution (Clopper-Pearson method) for CIs of proportions (24).

#### 11.1.2.2.3 Exploratory Statistical Analyses

For each serological method, the following may be performed as exploratory analyses:

- Describe the titers frequency of individual titers with possible non-parametric exploratory comparisons (robustness analysis, alternative to the GMT approach)
- Assess and quantify the second vaccination relative effect.
- Check any age-group heterogeneity.
- Confirm any gender effect on the immunogenicity parameters.

The exploratory analyses will be detailed in the Statistical Analysis Plan prior to the first database lock.

#### 11.1.2.2.4 Pre-booster Antibody Persistence

For each serological method, the statistical analysis will be restricted to:

- Proportion of subjects with detectable titer (for HI method: titer  $>10$  [turkey] or  $>8$  [horse] [1/dil] and for SN method: titer  $\geq 20$  [1/dil]) on D90, M3 and M6 or at M3, M6 and M12.
- GM of titers on D90, M3 and M6 or at M3, M6 and M12.
- Proportion of subjects with a HI titer  $\geq 40$  (turkey) or  $\geq 32$  (horse) (1/dil) on D90, M3 and M6 or at M3, M6 and M12.

The kinetics of the Ab titers assessed by HI, methods will be studied and summarized graphically:

- GM of anti-HA titers (HI method using horse or turkey erythrocytes) at M3 and M6 or at M3, M6 and M12 (*depending on the booster vaccination timing option*).

- GM of Ab titers (seroneutralisation method) at M3 and M6 or at M3, M6 and M12 (*depending on the booster vaccination timing option*).

#### **11.1.2.2.5 Booster Vaccination Immunogenicity**

For each serological method, HI (HI method using horse and turkey erythrocytes) and SN, the analysis will be similar to the primary statistical analysis (see Section 11.1.2.2.1) at M6 or M12 (booster vaccination) and M6+21 days or M12+21 days (*depending on the booster vaccination timing option*).

#### **11.1.2.2.6 Cellular Mediated Immune Response**

The analysis of the CMI response will be described in the Statistical Analysis Plan (SAP).

### **11.2 Population to be Analyzed**

#### **11.2.1 Definition of Populations**

##### **11.2.1.1 Immunogenicity Analysis Set**

The immunogenicity analysis set (IAS) is defined for the immunogenicity descriptive analyses of the primo-vaccination, the Ab persistence, and the booster vaccination.

The IAS is defined as the subset of subjects who received the first vaccine injection.

The analysis of the primo-vaccination (see Section 11.1.2.2.1) addresses endpoints involving pre- and post-injection titers at D0, D21 and D42 for HI, SN methods. The analysis will include all available data.

Data from subjects excluded from this analysis set will be listed separately and the reasons for exclusion, as well as the circumstances of the missing data, will be examined.

Additionally, for the booster analysis, the IAS is defined as subjects having also received the booster injection.

The analysis will be performed according to the randomized vaccine formulation group.

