## **2 Trial Objectives**

- To describe the safety profiles (injection site reactions and systemic events) during the 21 days following each injection (including the booster injection).
- To describe the immune response 21 days after the first and the second injection of each formulation.
- To describe the antibody persistence until the time of the booster vaccination at 6 or 12 monthsa after the first vaccination.

---

a The timing and dosage of the booster vaccination is dependent on the results of an ongoing study (GPA01). The possibilities of a booster at 6 or 12 months (and two flow-charts) are included as options, although by the time of protocol finalization the data from the ongoing study should be available and so it should be possible to decide on the booster timing and type during the protocol writing.

- To describe the immune response 21 days after a booster vaccination administered at 6 or 12 months after the first vaccination.

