#### 5.3.6.1 Conditions for Withdrawal

A subject may decide or a subject's parent/legal representative may decide for the subject to stop participating in the trial for any reason and at any time. In this case, the Investigator must determine that the reason for withdrawal is not related to an AE. The reason for a subject withdrawing during the trial will be specified in the source document and in the relevant section of the CRF.

Subjects/parents/legal representatives will be informed that they have the right to withdraw from the trial at any time.

The Investigator will discontinue the second or booster vaccination in the case of an event considered to be a definite contraindication (see following list). The vaccination will be delayed in the event of a temporary contraindication (see Section 5.3.5).

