##### **11.2.1.2 Per-Protocol Analysis Set**

Not applicable.

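### The D42 immunogenicity set requires only the first injection, so a child without the second dose who still gives a V05 sample would enter the post-dose-2 summaries

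*Protocol*

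**What the plan says.** - **Objective.** Protocol Section 2: "To describe the immune response 21 days after the first and the second injection of each formulation". The D42 titer is the only one that serves the second half of this objective.
- **Analysis set.** Section 11.2.1.1: "The IAS is defined as the subset of subjects who received the first vaccine injection". The primary-series analysis on this set "addresses endpoints involving pre- and post-injection titers at D0, D21 and D42 for HI, SN methods". Then: "The analysis will include all available data" and "The analysis will be performed according to the randomized vaccine formulation group". Table 11.1 assigns the IAS to the D0 to D42 period. Section 11.2.1.2 on the per-protocol set reads "Not applicable".
- **Booster set.** The same Section 11.2.1.1 adds: "Additionally, for the booster analysis, the IAS is defined as subjects having also received the booster injection".
- **Safety sets.** Section 11.2.1.3 forms a separate safety set for each dose from the children who received it. It also removes and lists separately the post-dose-2 safety results of a child whose two primary doses differed.
- **Stopping dose 2.** Section 5.3.6.1: "The Investigator will discontinue the second or booster vaccination in the case of an event considered to be a definite contraindication". The V03 procedures in Section 5.1.3 likewise say that the vaccination is not performed; they do not say that the child leaves the trial.
- **V05.** Section 5.1.3 orders serology at V05 for every subject. Figures 1 and 2 time that visit only from the second vaccination, at 21 days with a window of 3 days either side.

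**The concern.** For a child who did not receive the second injection, a response after that injection does not exist. The set definition nevertheless admits any D42 titer such a child supplies, under the randomized formulation, and no rule removes or separates it.

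The most exposed summaries are those that isolate the second dose: the D42/D21 ratios, the D21-to-D42 increase rates in Section 11.1.2.2.1, and the possible exploratory look at the relative effect of the second vaccination in Section 11.1.2.2.3. A one-dose child with a flat titer pulls the D42/D21 ratio toward 1 and, if one dose does less than two, lowers the D42 rates. The number of missed second doses need not be the same in every cell.

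At stake is whether the D42 figures describe what the objective names. No test, alpha or sample size depends on them.

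**Working it through.** **Step 1. The plan's own figure.** The only calculation in the protocol is the chance of seeing at least one AE of 1% incidence (Section 11.3). It reproduces: 1 − 0.99^240 = 0.910 (stated as above 90%) and 1 − 0.99^120 = 0.701 (stated as 70%). It does not use the IAS and is unaffected by this point.

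**Step 2. Can a one-dose child have a D42 titer?**
- For: Sections 5.1.3 and 5.3.6.1 stop the vaccination without ending participation, V05 serology is ordered for everyone, and the IAS takes whatever titer is available.
- Against: V05 has no scheduled date without a second vaccination, and after a related seizure Section 9.1.6 mentions only follow-up for safety.
- If no sample is drawn, nothing is mixed, because Section 8.1.3 does not replace missing titers (its only substitutions are for values outside the quantification limits).

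So the set permits mixing; the documents do not establish that it will occur.

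**Step 3. Size, if it occurs.** Inputs: 8 cells (Section 11.1.2.2.1) of 30 children (Synopsis, planned sample size). Let k be the number of one-dose children with a D42 titer in a cell. The protocol gives neither k nor any response rate, so the values below are assumptions.

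For a proportion, with two-dose rate p2 and one-dose rate p1, the mixed rate is ((30 − k)·p2 + k·p1)/30. It falls below p2 by k·(p2 − p1)/30:

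| Assumed p2 / p1 | k = 1 | k = 2 | k = 3 |
|---|---|---|---|
| 80% / 20% | 2.0 points | 4.0 points | 6.0 points |
| 60% / 20% | 1.3 points | 2.7 points | 4.0 points |
| 40% / 10% | 1.0 point | 2.0 points | 3.0 points |

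The most that one child can move a cell is 1/30 = 3.3 points.

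For a GMT, let R be the ratio of two-dose to one-dose GMT. The mixed GMT is the two-dose GMT times R^(−k/30):

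| Assumed R | k = 1 | k = 2 | k = 3 |
|---|---|---|---|
| 2 | 0.977 | 0.955 | 0.933 |
| 4 | 0.955 | 0.912 | 0.871 |
| 8 | 0.933 | 0.871 | 0.812 |

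The same arithmetic applies to the D42/D21 ratio. If the two-dose ratio is 4 and two children are flat, the cell shows 4^(28/30) = 3.65.

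**Step 4. Against the precision of a cell.** Suppose two one-dose non-responders and 22 responders among the other 28. The IAS gives 22/30 = 73.3% (exact 95% CI 54.1% to 87.7%). Children given dose 2 give 22/28 = 78.6% (59.0% to 91.7%). The gap of 5.2 points is well inside either interval.

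**The case against.** Four counter-arguments carry weight.

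1. *The mechanism is not shown.* The stopping rule sits under a heading about withdrawal, the seizure rule speaks only of safety follow-up, and V05 cannot be scheduled without a second vaccination. The V05 instruction to sample everyone is a routine visit step, not written with these children in mind. This stands. A reader might infer that such children will be analysed as if they had received the second dose; the documents do not support that. They leave open whether the sample exists, and an as-randomized set does not claim that every member received both doses.

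2. *An as-randomized summary using all available data is legitimate, and restricting to dose-2 recipients conditions on an event after randomization.* Definite contraindications include a related SAE, so the restriction is not neutral. This stands too, and is why both tables are needed.

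3. *The booster comparison is loose.* The booster is a separate stage with its own pre-injection baseline, whereas D0 to D42 is one series. This stands in part: a reader might see a flat contradiction between doses, which goes too far. The per-dose safety sets, however, do condition on dose 2 within the primary series.

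4. *The rest can go to the SAP.* Listings and exploratory detail can. The analysis sets themselves are fixed in protocol Section 11.2.

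It is also tempting to infer that the booster results would be contaminated by singly primed children. The same contraindications are checked again before the booster, so only a child whose reason had resolved could get there.

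**Conclusion.** The point holds as a mismatch between the D42 analysis set and the stated objective. By definition the set would include any D42 titer from a child without the second injection, and nothing separates it.

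The consequence is descriptive and probably small. Under the assumed rates it is about 1 to 2 percentage points per such child in a cell of 30, and for a few children it lies inside the confidence interval. It rests on two things the protocol does not give: how many children miss the second dose yet have a D42 titer, and how far one-dose and two-dose responses differ. A reader might infer that the D42 results will be materially biased; that would need many such children in a cell, and nothing in the document points to that. This is an inexpensive improvement, not a flaw that undermines the trial.

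**What to change.** In Section 11.2.1.1 and Table 11.1:

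- Present D42 titers, D42/D0, D42/D21 and D42 seroconversion or significant increase on IAS subjects who received the second injection, following the pattern already used for the booster.
- Keep the all-IAS, as-randomized table alongside.
- List separately the D42, persistence and booster results of children with only one primary dose.

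Separately, reconcile the V05 instruction to sample every subject (Section 5.1.3) with the V05 timing that depends on the second vaccination (Figures 1 and 2), for children who did not receive it. No visit date is proposed here; that is for the sponsor and the investigators.

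The cost is wording in one section, one table and the visit schedule. The downside is a slightly smaller D42 denominator and conditioning on a post-randomization event, which the retained all-IAS table offsets.
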